### 9.2 Serum and Tissue Biomarkers

Exploratory molecular correlative analyses will be conducted on serial tumor and plasma specimens to identify biomarkers predictive of patient outcome and investigate sorafenib-induced changes in the circulation of pro-angiogenic factors and tumor signal transduction pathways (**see section 1.8 for study rationale**). Plasma will be collected for measurement of a panel of angiogenic markers that includes, but is not limited to, VEGF, OPN, PDGF, bFGF, IL-8 and IL-6 at baseline, 1 – 3 weeks after completion of combined neoadjuvant sorafenib/RT treatment, and then 1 – 3 weeks before surgical resection of the tumor (approximately 3 – 7 weeks following completion of sorafenib/RT). Blood samples (10 mL) will be drawn using venipuncture into a Vacutainer containing potassium EDTA and inverted gently several times to mix with anticoagulant. Within 10-15 minutes after collecting, blood samples will be centrifuged in a refrigerated (4°C) centrifuge for 10 minutes to separate the plasma. If a refrigerated centrifuge is not available, the tubes should be chilled in an ice bath for 5-15 minutes and then placed in a standard centrifuge for 10 minutes to separate the plasma. The plasma will be transferred to polypropylene tubes and frozen at -70°C or lower. The tubes will be labeled with the study number, and subject's study number, and time and date of the sample acquisition.

Fresh tumor tissue will be collected at baseline (pre-treatment with sorafenib/RT), and then at time of surgical resection on approximately study day 50 – 90. Tissue will be immediately frozen with liquid nitrogen and stored at -70°C or lower. Tumor tissue will be mechanically homogenated for 5 minutes on ice in 1 ml of extraction buffer per 100 mg tissue wet weight, and extract obtained after centrifugation for 20 minutes at 4°C will be transferred to polypropylene tubes and frozen at -70°C or lower. The tubes will be labeled with the investigator's name, study number, and subject's study number, and time and date of the sample acquisition. Multiplex analysis using Luminex technology and/or ELISA for VEGF, sVEGFR2, and bFGF will be performed on plasma and tumor extracts using commercial kits. Manufacturers' protocols will be followed and samples are to be measured in duplicate. Changes in activation states of MAPK signal transduction intermediaries (pERK) will be evaluated by Western blotting.

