### 10.5 Specimen Submission for Molecular Correlative Studies

With the patient's consent, tissue and blood specimens will be submitted as outlined below.

- Paraffin-embedded tissue blocks or slides from the time of diagnosis (prior to therapy) and at the time of surgical resection will be submitted for expression of relevant molecular targets. 1-2 paraffin-embedded tissue blocks containing formalin-fixed tumor tissue should be submitted for evaluation and expression of mutations in relevant molecular pathways. Paraffin blocks should be processed according to standard institutional protocols. If blocks are unavailable, 16 unstained slides are acceptable alternatives.
- Two blood specimens will be collected from each patient prior to treatment (2 x 10 mL). Subsequent blood specimens (1 x 10 mL) will be collected at selected intervals as indicated in the study calendar (see section 10.1, weeks 2, 6, 9, and end of study). In the event that a patient is removed from the study, a blood specimen (approximately 10 mL) will be obtained at the time the patient is removed from protocol treatment.

One blood specimen should be collected in a 10 mL purple-top (EDTA) tube, inverted several times, and placed on wet ice until centrifugation. The tube should be centrifuged as soon as possible at approximately 1,000 to 1,500 rpm for 10 minutes. Plasma should be removed and placed in 1 mL aliquots in labeled cryotubes. Buffy coat cells should be separately removed and placed in labeled cryotubes. All specimens must be labeled with protocol number, patient registration number, and date of specimen collection. All tubes are then to be frozen (snap frozen with liquid nitrogen if possible) and stored at -70°C until shipped to the laboratory on dry ice as detailed below.

The second blood specimen should be collected in a 10 mL red-top tube, allowed to clot at room temperature for 30 minutes, and placed on wet ice until centrifugation. The tube should be centrifuged at 3000 rpm for 10 minutes. Serum should be removed and placed in 1 mL aliquots in labeled cryotubes. All specimens must be labeled with protocol number, patient registration number, and date of specimen collection. All tubes are then to be frozen (snap frozen with liquid nitrogen if possible) and stored at -70°C until shipped to the laboratory on dry ice as detailed below.

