### 11.4.3 Distant Disease-Free Survival

Defined as the duration of time from registration until development of distant metastatic disease or death, whichever occurs first.

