### 11.4.5 Progression-Free Survival

Defined as the duration of time from registration to progressive disease, local recurrence, distant metastatic disease, or death, whichever occurs first.

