### 11.4.6 Overall Survival

Defined as the interval of time from registration until death from any cause.

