### 13.2 Secondary Objectives

13.2.1 To determine the rate of R0 (negative resection margin), R1 (microscopically positive resection margin), and R2 (macroscopically resection margin) following neoadjuvant conformal radiotherapy in combination with sorafenib.

13.2.2 To analyze changes in tumor blood flow, blood volume, capillary permeability, and cell viability pre- and post-treatment with combined sorafenib/RT using dynamic contrast-enhanced MRI. The primary endpoints of these studies will be the transfer constant (Ktrans) and the initial area under the gadolinium concentration time curve (IAUGC, mMgD°min—see **section 9.1 for DCE-MRI imaging protocol**).

To account for within-subject correlation, we will use a mixed effects model to analyze changes in DCE-MRI pharmacokinetic parameters (Ktrans and ve) at baseline and then following neoadjuvant sorafenib/RT. These

comparisons will be made within the framework of the mixed effects model. Galbraith et al. reported the mean (range) to be 0.43 ml/ml/min (0.07-1.03) for  $K^{\text{trans}}$  and 32.2 ml/ml (12.9-62.4) for  $v_e$  among human tumors. If we assume that the range represents  $\pm 2$  SD, SD is approximately 0.24 for  $K^{\text{trans}}$  and 12.38 for  $v_e$ . A sample size of 25 patients will provide 71% power to detect a 1.0 standard deviation change in  $K^{\text{trans}}$  and  $v_e$  between these two time points.

13.2.3 To initiate analyses of molecular markers of tumor response assessment comparing (1) a microarray of a panel of serum angiogenic markers pre- and post-treatment; and (2) immunohistochemistry of tumor tissue pre- and post-treatment for expression of angiogenic proteins (VEGF, VEGFR1-3), growth factors correlated with hypoxia and resistance to radiation (EGF, FGF, HIF-1 $\alpha$ ), and modulators of proliferation and signal transduction (Ki-67, pERK). These analyses will be conducted in an exploratory manner with the aim of generating clinically and biologically interesting hypotheses. We will correlate pre- and post-treatment tissue and plasma biomarker levels (as well as the pre- and post-treatment changes) with DCE-MRI parameters and clinical outcomes. A regression analysis will be used to assess a correlation with DCE-MRI parameters. Logistic regression analysis will be used for binary clinical outcomes (e.g.,  $\geq 95\%$  necrosis) and Cox regression analysis will be used for time-to-event outcomes.

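### Cox models of PFS and distant DFS on post-treatment markers start the clock at registration, so a progression found before surgery can precede the marker said to predict it

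*Protocol*

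**What the plan says.** Protocol 13.2.3 sets the covariates: "We will correlate pre- and post-treatment tissue and plasma biomarker levels (as well as the pre- and post-treatment changes"), to be related to DCE-MRI parameters and clinical outcomes. For the outcome models it says "Cox regression analysis will be used for time-to-event outcomes". It calls this work exploratory and hypothesis-generating. It states no landmark, delayed entry or time-dependent covariate. Section 13.2.4 refers to 11.4 for the time-to-event definitions.

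Section 11.4 uses two time origins:

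- From registration: PFS ("Defined as the duration of time from registration to progressive disease, local recurrence, distant metastatic disease, or death, whichever occurs first"), distant DFS ("Defined as the duration of time from registration until development of distant metastatic disease or death, whichever occurs first") and OS ("Defined as the interval of time from registration until death from any cause").
- From resection: time to local recurrence, local DFS and DFS (11.4.1, 11.4.2, 11.4.4).

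Section 9.2 gives the sampling times. Post-treatment tissue is taken "at time of surgical resection on approximately study day 50 – 90". Post-treatment plasma is drawn 1–3 weeks after sorafenib/RT ends and again 1–3 weeks before surgery. The calendar in 10.1 places tumour imaging and chest CT in the week 7–9 column, before surgery. Progression is a listed reason to stop treatment (7.7), and a new lesion counts as progressive disease (11.3.1). Section 10.5 adds a draw: "In the event that a patient is removed from the study, a blood specimen" is taken when protocol treatment ends.

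**The concern.** Section 9.2 gives the aim as finding markers that predict how patients fare. A Cox model reads that way only if the covariate is known before the risk period begins. For PFS and distant DFS, the post-treatment level and the change are measured weeks to about three months after time zero, and the protocol foresees events inside that gap. If progression changes the marker, the model partly tests whether markers differ after progression. With about 25 patients, two or three such cases can move the result. Misleading leads are the main harm here, because the purpose is to choose hypotheses for later work.

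**Working it through.** The plan gives no figure for this analysis, so there is none to reproduce. The check has three parts.

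**1. Timing.** RT takes about 35 days (7.4) and surgery follows 3–7 weeks later (7.5). Day 1 is the start of RT, so the gap from registration is slightly longer than these days suggest.

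- Resection: 35 + 21 = day 56 to 35 + 49 = day 84, in line with the stated day 50–90.
- First post-treatment plasma: 35 + 7 = day 42 to 35 + 21 = day 56.
- Later plasma: 56 − 21 = day 35 to 84 − 7 = day 77.
- Restaging in weeks 7–9: day 43 to day 63.

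Restaging comes before resection tissue. It may fall before or after the later plasma draw. The first plasma draw usually precedes or coincides with it, since the calendar places the week 6–8 blood test one column earlier.

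**2. Direction and rough size.** In a one-covariate Cox model, each event contributes to the score, at zero effect, the marker of the patient with the event minus the mean marker of those at risk. Take 25 patients, 2 early progressors (8%) and a 1 SD shift caused by progression. Their expected contributions are 1 − 2/25 = 0.92 and 1 − 1/24 = 0.96, sum 1.88; without a shift both would be 0. With a 50% event rate among the other 23 there are about 2 + 11.5 = 13.5 events, so the score has SD of about √13.5 = 3.67. The test statistic moves by 1.88/3.67 = 0.51, and P(|Z + 0.51| > 1.96) ≈ 0.074 + 0.007 = 8%. This treats the number of progressors as fixed and the marker variance as 1.

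**3. Simulation.** Two set-ups were used, both with n = 25 (13.1.2). Assumed, because the documents do not say: the share progressing before sampling, the marker shift that progression causes, a 50% five-year event rate afterwards, and a marker value for every progressor. The marker has no true predictive value.

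- Set-up A: sampling at 2.3 months, early progression at 1.6–2.2 months, score test, 6,000 trials per cell.
- Set-up B: sampling uniform on day 50–90, early progression at 60–100% of that time, Wald test, 3,000 trials per cell.

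At a true 5%, simulation error is √(0.05 × 0.95/6,000) = 0.3 points for A and √(0.05 × 0.95/3,000) = 0.4 points for B.

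Rejection rate of a nominal 5% test, clock from registration:

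| Early progressors | Set-up | No shift | 0.5 SD | 1 SD | 1.5 SD |
|---|---|---|---|---|---|
| 4% | A | – | – | 7.1% | 9.1% |
| 5% | B | 4.6% | 5.5% | 7.4% | 10.1% |
| 8% | A | – | – | 9.5% | 15.2% |
| 10% | B | 5.0% | 6.7% | 11.2% | 17.7% |
| 12% | A | – | – | 13.2% | 23.2% |
| 16% | A | – | – | 18.6% | 31.4% |
| 20% | B | 5.3% | 8.4% | 21.6% | 38.5% |

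In B with a 1 SD shift, the median hazard ratio per SD for this null marker is 1.10, 1.21 and 1.36 at 5%, 10% and 20% early progressors. With the clock started at the sample in event-free patients, rejection is 5.3–5.6% in A (run for the 1 SD shift) and 4.5–5.6% in B, with hazard ratios of 0.98–1.02.

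For OS with no death before sampling, a null marker is rejected in 4.1% of 2,000 trials under either origin.

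**The case against.** The strongest reply is that 13.2.3 names no particular outcome or entry rule, that such detail may sit in a statistical analysis plan not shown here, and that DFS from resection already suits tissue markers. Much of this stands. Missing detail is not the fault, and the resection-origin outcomes are sound for tissue. But the protocol itself fixes the post-treatment covariates and the registration origin of PFS and distant DFS, and it does not keep the two apart.

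The exploratory label also stands: no error rate is claimed for these models and no trial decision depends on them. That lowers the severity but does not restore the time order.

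A reader might go further in four ways that the documents do not support:

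- **OS is biased in the same way.** A death cannot come before a marker and alter it, and a marker shifted by progression may truly predict later death. The origin makes no practical difference unless patients die before sampling.
- **All post-treatment plasma is affected.** The first draw usually precedes or coincides with restaging.
- **Blood drawn at removal is the post-treatment level.** Section 10.5 collects it, but neither 9.2 nor 13.2.3 says that it is used that way. The text leaves this open.
- **The larger rates in the table apply to this trial.** No document figure supports 16–20% early progressors or a 1.5 SD shift. For tissue, a progressor who is not resected has no specimen and drops out of the model, so giving every progressor a value overstates the bias.

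**Conclusion.** The point holds for PFS and distant DFS modelled on resection tissue, on the later pre-surgery plasma, and on changes computed from either. As written, the covariate can postdate the event. Its size in this trial is unknown. Under the stated assumptions with a 1 SD shift, the false-positive rate is about 7% with 4–5% early progressors (about one patient in 25) and about 10–11% with 8–10% (two to three patients). It stays near 5% if progression does not move the marker. The primary endpoint, the safety rule, the Kaplan–Meier estimates and the baseline-marker models are untouched. This is a low-severity improvement to an exploratory analysis, worth making because it is cheap.

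**What to change.** In 13.2.3:

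1. Keep registration as time zero for Cox models of baseline markers.
2. For post-treatment levels and changes, start the PFS and distant-DFS models at the sample date (resection for tissue, draw date for plasma) and include only patients still event-free then. For tissue, DFS from resection as already defined in 11.4.4 is an alternative.
3. State that blood drawn at removal for progression is not used as the post-treatment level in these models.
4. Report separately the events and dropouts that occur before the landmark.

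The cost is a wording change, with no new patients, samples or visits. The downside is that the few earlier events leave these models, which then describe outcome from sampling rather than from registration.

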### 1.4 Anti-Angiogenic Agents and RT

There are limited data examining the combination of RT and anti-angiogenic agents, particularly in STS. Pre-clinical data suggest a significant synergistic effect when anti-angiogenic targeted therapies, such as sorafenib, are combined with RT. Overproduction of angiogenic factors in the tumor vasculature leads to disordered/poorly regulated tumor perfusion. Delivery of anti-angiogenic agents appears to “normalize” the tumor micro-environment with subsequent enhanced efficacy of cytotoxic treatments on tumor tissue.

This mechanism is particularly relevant for RT since hypoxia is a crucial mediator of resistance to this therapeutic modality.

Preliminary clinical data in rectal cancer and malignant brain tumors have demonstrated promising results for the combination of anti-angiogenic agents and RT with respect to downstaging of the primary tumor, local control, and improved progression-free survival. Although tumors may change little in overall size with targeted agents, pathologic analysis frequently demonstrates significant tumor necrosis, and in some cases no viable residual tumor may be present. These findings are significant for STS since complete (100% tumor necrosis) or near-complete ( $\geq 95\%$  tumor necrosis) pathologic response has been observed, in a retrospective analysis, to correlate with improved local, distant, and overall survival in STS patients treated with neoadjuvant chemoradiotherapy using doxorubicin and ifosfamide.

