### 1.7 Dynamic Contrast-Enhanced Magnetic Resonance Imaging

Variability in specific patient and tumor molecular factors likely influences the response or resistance of individual patients to treatment. Consequently, novel methods for evaluating and monitoring tumor response to therapy are needed beyond that of traditional tumor growth or shrinkage. Progress in this arena will enable novel anti-cancer therapies to be individualized for patients in a rational manner to maximize the benefit-to-risk ratio.

A major challenge facing studies of anti-angiogenic therapies is the detection of meaningful drug response in the early-phase after drug introduction. Treatment with these agents is not commonly associated with significant radiographic tumor shrinkage, and no standard surrogate markers for response to these therapies exist. One potential avenue for monitoring activity is functional imaging modalities that can detect changes in blood flow, vessel wall permeability, or metabolic activity that may occur quickly. Dynamic contrast-enhanced magnetic resonance imaging (DCE-MRI) is one such approach that can evaluate changes in the tumor vasculature. In this technique, MRI is used to track bolus injections of paramagnetic gadolinium chelate contrast reagent as it passes through the tumor tissue. Concentration time curves are modeled based on signal intensity data in the region of interest. Quantitative values, such as the volume transendothelial transfer constant ( $K^{\text{trans}}$ ) and the extravascular leakage space ( $v_e$ ), are then determined. Vascularized tumor volume can then be obtained by summing voxels, and histogram and principal components analysis can be employed to assess regional and chronologic change.

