#### 4.0 ACCRUAL GOAL

- Phase I— Dose-escalation schedule comprising 6 to 12 patients (see schema). This sample size is based on a traditional 3+3 cohort design with escalating doses of sorafenib in combination with 50 Gy of conformal radiotherapy delivered in 25 fractions (200 cGy per fraction). Based on preclinical data regarding the radiobiology of sorafenib, sorafenib will be initiated at a dose of 200 mg twice daily, followed by 200 mg Q AM/400 mg Q PM for the 2nd cohort, followed by 400 mg bid for the 3rd cohort. Since 400 mg bid is the well established MTD for sorafenib monotherapy in patients with renal cell carcinoma and hepatocellular carcinoma, the dose will not be escalated above this level even if DLT is not observed. Dose level escalation will be determined based on DLTs observed from initiation of sorafenib/RT until time of surgery.
- Phase II— anticipated number of 25 patients will be enrolled depending on phase I result. Anticipating an improvement in near-complete pathological response ( $\geq 95\%$  tumor necrosis) from 0% with RT alone to 33% with combined sorafenib and RT, we will have an 80% power to detect this difference if we accrue 25 patients, assuming a type I error rate of 5%.

Total target accrual is 30-35 patients depending on results of dose-escalation schedule from Phase I of trial.

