### 13.1.2 Phase II Trial

The primary endpoint of the phase II trial will be the rate of complete/near-complete pathologic response ( $\geq 95\%$  tumor necrosis) following treatment with this multimodality therapy. Anticipating an improvement in the pathological complete/near-complete response rate from 10% with RT alone to 33% with combined sorafenib and RT, we will have an 80% power to detect this difference if we accrue 25 patients, assuming a type I error rate of 5%.

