13.2.4 To obtain preliminary data regarding local disease control, distant disease control, progression-free survival, and overall survival with this novel therapeutic regimen. Kaplan-Meier method will be used to estimate time-to-event measures. For definitions of time-to-event measures, see Section 11.4

13.2.5 To determine the rate of radiographic response to neoadjuvant sorafenib/RT. Cross-sectional radiographic response will be evaluated by RECIST criteria (**see section 11.3**). Categorical differences in these data (complete response, partial response, stable disease, and progressive disease) will be tested against pathologic response categories using the Chi-squared/Fisher's exact test.

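### Section 13.2.5 relates radiographic to pathologic response only through categories; the table is likely to be sparse and the test weak at N = 25, although both measures are recorded as continuous values

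*Protocol*

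**What the plan says.** Section 13.2.5 has as its objective the rate of radiographic response. It then adds a comparison: "Categorical differences in these data (complete response, partial response, stable disease, and progressive disease) will be tested against pathologic response categories", by the chi-squared or Fisher's exact test. It states no power for this test, names no other comparison of the two measures, and does not define the pathologic categories. The protocol's main cut-point elsewhere is ≥95% necrosis.

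Two background statements bear on how the RECIST categories will fill. Section 1.7 says of anti-angiogenic agents: "Treatment with these agents is not commonly associated with significant radiographic tumor shrinkage". Section 1.4 begins a sentence with "Although tumors may change little in overall size with targeted agents" and goes on to say that pathologic examination often shows substantial necrosis all the same.

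Both measurements exist before they are categorised. Section 11.2 records the longest diameter of the single target lesion. Section 7.6 has the pathologist record percent necrosis per slide and average it over slides. Partial response needs a fall of at least 30% in longest diameter (Section 11.3.1).

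**The concern.** If most tumors change little in diameter, most patients fall in the stable-disease row and few are left to carry any association. The test then has little chance of a positive result even when diameter change and necrosis are truly related. Categorising also discards information that the trial has already collected.

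At stake is how a null result is read. Section 1.7 already doubts tumor size as a marker for these agents. A non-significant table could be cited as evidence that RECIST does not track necrosis when the analysis had little ability to show that it does.

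**Working it through.** The protocol states no figure for this test, so there is none to reproduce.

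**Inputs from the protocol**
- Phase II size: "anticipated number of 25 patients will be enrolled depending on phase I result" (Section 4.0).
- Size if Phase I patients are pooled: "Total target accrual is 30-35 patients depending on results of dose-escalation schedule" (Section 4.0).
- Anticipated ≥95% necrosis: "from 10% with RT alone to 33% with combined sorafenib and RT" (Section 13.1.2), so 0.33 × 25 ≈ 8 responders.
- Level: 5%, stated in Section 13.1.2 for the primary endpoint only. Two-sided 0.05 is assumed here.

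**Assumptions, not in the protocol**
- Pathology split at 95%, and RECIST collapsed to stable versus not stable.
- The share of patients outside stable disease, and the correlation between shrinkage and necrosis.

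**Step 1. Smallest attainable p-value (no effect size needed).** With R = 8 responders in N = 25 and k patients outside stable disease, the most extreme table has all k among the responders. Its probability is C(8,k)/C(25,k), and here that is also the two-sided p.
- k = 1: 8/25 = 0.32
- k = 2: 28/300 = 0.093
- k = 3: 56/2300 = 0.024. If only two of the three are responders, p = (56 + 28×17)/2300 = 532/2300 = 0.23.

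So with one or two patients outside stable disease the test cannot reach 0.05, and with three it does so only if all three are responders. The two-patient limit also holds for pooled data: minimum p is 0.103 at N = 30 (10 responders) and 0.111 at N = 35 (12 responders).

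The limit depends on the number of responders. At N = 25 with 7 responders the two-patient minimum is 21/300 = 0.07, but with 6 it is 15/300 = 0.05, which just reaches the level.

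**Step 2. How often two or fewer would occur.** For X ~ Binomial(25, q), P(X ≤ 2) = (1−q)^25 + 25q(1−q)^24 + 300q²(1−q)^23. This is 0.87 at q = 5%, 0.54 at 10%, 0.10 at 20% and 0.01 at 30%.

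**Step 3. Power.** Simulation with 2000 runs per setting: shrinkage and necrosis bivariate normal with correlation ρ, the top 33% on necrosis counted as pathologic responders, and the top q on shrinkage counted as outside stable disease. N = 25, two-sided 0.05.

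| ρ | Fisher, q = 5% | q = 10% | q = 20% | q = 30% | Rank-sum, diameter change by ≥95% necrosis | Spearman |
|---|---|---|---|---|---|---|
| 0.4 | 2% | 8% | 14% | 17% | 29-30% | 46% |
| 0.5 | 3% | 12% | 22% | 26% | 45-47% | 68% |
| 0.6 | 5% | 17% | 34% | 39% | 64-66% | 87% |
| 0.7 | 6% | 24% | 47% | 58% | 81-83% | 97% |

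At N = 35, over the same range of ρ, Fisher gives 6-17%, 14-45%, 22-67% and 23-74% for the four shares, and Spearman about 62-99%.

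**Step 4. Exact Fisher power without the normal model.** N = 25, with assumed partial-response rates in pathologic responders and non-responders:
- 10% and 0%: 3%
- 20% and 0%: 18%
- 30% and 5%: 25%
- 40% and 5%: 45%
- 50% and 5%: 64%

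**Step 5. The chi-squared option.** With 8 of 25 responders, the expected responder count in a RECIST row of k patients is 8k/25. For this to be at least 5, k must be at least 16, and two such rows need 32 patients. The usual expected-count criterion therefore cannot be met at N = 25, however RECIST is distributed.

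**The case against.** A reader might infer that the protocol itself expects nearly all patients to be stable disease, and so that the test has almost no power. The documents do not support that. The remarks in Sections 1.4 and 1.7 are qualitative, concern targeted or anti-angiogenic agents in general, and give no rate. Section 1.4 also cites promising downstaging when such agents are combined with radiotherapy, and the Synopsis hypothesises a smaller resected volume. Progressive disease, including progression by a new lesion, also counts as outside stable disease (Sections 11.3.1 and 11.3.2), and chest CT is repeated before surgery. Power is 14-58% if 20-30% of patients are outside stable disease, and about 64% under a strong contrast in partial response (50% against 5%).

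It can also be said that Fisher's test is already named for sparse cells, that the objective is a response rate, and that no power is claimed. All of that stands. The comparison is nevertheless a stated choice, and unlike the biomarker work in Section 13.2.3 it is not labelled exploratory.

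The strongest point concerns the replacement. Sections 1.5 and 1.8 treat ≥95% necrosis as the clinically meaningful threshold, whereas Spearman gives weight to differences below it. A diameter measure also misses progression by new lesions. The normal model favours a correlation test too, since real necrosis values are bounded at 100% and may tie. The continuous analysis should therefore accompany the RECIST table. The rank-sum comparison keeps the 95% threshold and still has more power than Fisher in every simulated setting.

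**Conclusion.** The point holds as a likely loss of power in a secondary comparison; Section 13.2.5 contains no false statement. One part needs no assumed effect size: with 8 responders in 25, split at 95% necrosis, two or fewer patients outside stable disease make significance impossible. The rest is conditional. Power is close to zero if about 5% are outside stable disease, low at 10%, and low to moderate at 20-30%, whereas the rank correlation has about 46-97%. The shares, the correlations and the normal model are assumptions, and all simulated patients outside stable disease were on the shrinkage side, so progression was not modelled.

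A reader might also infer that the test cannot show an association at all. That is so only at the very sparse end. Nor does the protocol say that it would read a null table as evidence against RECIST; that is a risk to guard against. The primary endpoint and the radiographic response rate are unaffected, and the change is desirable but not essential.

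**What to change.** In Section 13.2.5:

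- Add as the inferential comparison the percent change in longest diameter, baseline to the pre-surgical scan, against percent necrosis: Spearman correlation with a confidence interval.
- Compare the same diameter change between patients with ≥95% and <95% necrosis by the Wilcoxon rank-sum test, so that the protocol's own threshold is kept.
- Keep the RECIST-by-pathology table as descriptive, with Fisher's exact test only. State the pathologic categories used, and list progression by new lesions separately.
- State that a non-significant categorical result will not be taken as evidence that RECIST fails to track necrosis.

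The cost is wording and one or two extra analyses. Both variables are already collected, so no patients, visits or measurements are added. The small downside is that the correlation gives weight to necrosis differences below 95%, which the rank-sum comparison offsets.
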